### Missing primary outcome data

A sensitivity analysis using a variety of imputation methods to impute any missing primary outcome data (6-month EORTC QLQ-C30^31^ global health status/QoL score) will be performed. The imputation methods will include last observation carried forward, regression and multiple imputation. The estimates of the treatment effect and its associated CI, from the various imputation methods, will be graphically displayed alongside the results for the observed data.

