### Sample size calculation

The primary endpoint will be the global health status/QoL scale (questions 29 and 30 of the EORTC-QLQ-C30)^31^ at 6 months post baseline. Assuming an SD of 21 points for the global health status/QoL scale and a mean difference of 7 or more points on the global health status/QoL scale between the groups is of clinical/practical importance (a ‘small’ standardised effect size of 0.33). With no allowance for clustering; for the PET versus surgery DESI comparison with 190 eligible women per group we will have a 90% power of detecting this difference or more as statistically significant between the groups at the 5% two-sided level. If we assume an intraclass correlation of 0.03 then allowing for the clustered RCT design we will need to recruit 10 women, eligible for using the decision aids, per cluster (ie, 50 clusters × 10 women), 500 in total (this assumes a design effect of 1.3). With a 20% loss to follow-up by 6 months we need to recruit 13 women per cluster (50 clusters × 13 women) or 650 in total (325 per group).

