### Data analysis

The statistical analyses will be performed on an intention-to-treat basis comparing the DESI and control groups. All statistical exploratory tests will be two tailed with p=0.05. Baseline demographics (eg, age), physical measurements and health-related QoL data will be assessed for comparability between the treatment groups. A marginal generalised linear model (GLM), with coefficients estimated using generalised estimating equations (GEE) with robust SEs and an exchangeable autocorrelation matrix in STATA will be used to analyse the outcomes and allow for the clustered nature of the data. The exchangeable correlation structure corresponds to an equal correlation model, meaning that the correlations of the outcomes with a cluster, that is, breast centres, are the same. For continuous outcomes, such as mean global health status/QoL score (questions 29+30 of EORTC QLQ-C30^31^) at 6 months postdiagnosis/consent intervention, knowledge score and preference for treatment score, an identity link with a normal distribution for the outcome will be used. Estimates for the treatment group coefficient from this regression model will be reported along with their associated 95% CI. In the event of differences between the intervention and control groups with respect to baseline demographic, physical and health-related QoL measurements, then these covariates will be used in the GLM to adjust the treatment effect for these variables. The adjusted regression coefficient estimate for the treatment group parameter along with its 95% CI will then be reported.

For the other secondary outcomes, at 6 weeks and 6 months, such as the other dimensions of the EORTC QLQ C30,^31^ the EORTC QLQ-BR23^36^ and EORTC QLQ-ELD14,^37^ the mean QoL dimension scores will be compared between the intervention and control groups using similar models.

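### LOCF and single regression imputation stand unranked beside multiple imputation as checks on missing 6-month QoL: the first is generally biased, the second can give intervals that are too narrow, and no listed method tests a controlled departure from missing-at-random

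*Protocol article*

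**What the plan says.** The primary endpoint is the EORTC QLQ-C30 global health status/QoL score at 6 months. Under *Sample size calculation* the protocol article plans "With a 20% loss to follow-up by 6 months" and recruits 650 women to allow for it. Under *Data analysis* the outcome model is a marginal linear model fitted by "generalised estimating equations (GEE) with robust SEs and an exchangeable autocorrelation matrix in STATA", with baseline covariates added if the arms differ at baseline.

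The section *Missing primary outcome data* places all imputation in a sensitivity analysis: "The imputation methods will include last observation carried forward, regression and multiple imputation". The resulting estimates and confidence intervals "will be graphically displayed alongside the results for the observed data". The article does not use the term complete case, but this wording implies that the main estimate comes from women with an observed 6-month score. It does not rank the three methods, and it does not say whether regression imputation is deterministic or stochastic.

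The same QoL scale is also collected at baseline and at 6 weeks (*Primary outcome measure*; Table 1).

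**The concern.** The three named methods are not of equal standing.

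- **LOCF** assumes that a woman's score would not have moved since her last questionnaire. A carried baseline score contains none of the intervention's effect. A carried 6-week score reflects early treatment and recovery, and treatment choice is one of the things the intervention is meant to influence.
- **Regression imputation**, listed separately from multiple imputation, most naturally means single imputation. If predicted means are filled in and analysed as data, the standard error is too small.
- **Multiple imputation** is valid under missing-at-random and carries the imputation uncertainty into its interval.

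A reader of the planned graph would see a biased estimate and an interval that is too narrow beside valid results, with nothing to tell them apart. If all the results agreed, the reader could take this as robustness in general. None of the listed methods varies the missing-at-random assumption by a stated amount, so agreement could not support that conclusion.

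**Working it through.** **Inputs from the protocol article (*Sample size calculation*).** SD 21 ("Assuming an SD of 21 points for the global health status/QoL scale"); target difference 7 points; 5% two-sided; 90% power; intraclass correlation 0.03; 50 units; 20% loss.

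**The plan's own figure.** n per arm = 2 × (1.960 + 1.282)² × (21/7)² = 189.1, rounded up to 190, as stated ("with 190 eligible women per group we will have a 90% power of detecting this difference"). The design effect is 1 + 9 × 0.03 = 1.27, stated as 1.3. Then 380 × 1.3 = 494, rounded to 50 × 10 = 500. For loss, 10/0.8 = 12.5, rounded up to 13 per unit, or 650. The sample size reproduces. At 20% loss, 130 of 650 scores are missing and 520 are observed.

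**LOCF.** With equal loss in both arms and missingness unrelated to outcome, the expected difference is 0.8 × 7 + 0.2 × d, where d is the between-arm difference in the carried scores.

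- Baseline carried, d = 0: 5.6 points.
- 6-week score carried with half the effect, d = 3.5 (assumption): 5.6 + 0.7 = 6.3 points.
- 6-week score carried with the full effect, d = 7 (assumption): 7.0 points.

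**Deterministic regression imputation.** Let r be the correlation between predictor and outcome. The documents do not give it, so a range is assumed. At 20% missing:

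- variance factor that the software reports: 0.8 + 0.2r²
- true variance factor: (1 − r²)/0.8 + r²
- SE ratio = square root of reported/true; error rate = 2 × [1 − Φ(1.96 × ratio)]

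| r (assumed) | Reported | True | SE ratio | Two-sided error rate | Coverage |
|---|---|---|---|---|---|
| 0.3 | 0.818 | 1.2275 | 0.816 | 11.0% | 89.0% |
| 0.5 | 0.850 | 1.1875 | 0.846 | 9.7% | 90.3% |
| 0.6 | 0.872 | 1.1600 | 0.867 | 8.9% | 91.1% |

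**Simulation with clusters.** 50 units × 13 women, intraclass correlation 0.03, SD 21, true difference 7, about 20% missing, 1,500 runs. Assumptions not in the documents: baseline to 6-month correlation 0.5, mean decline of 5 points, last observation = baseline, and cluster-robust linear regression in place of GEE. Each cell gives the mean estimate and the coverage of the nominal 95% interval.

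| Missingness | Observed data | LOCF | Deterministic regression | Multiple imputation |
|---|---|---|---|---|
| Completely at random | 7.08 (94.6%) | 5.67 (88.8%) | 7.08 (88.9%) | 7.08 (93.6%) |
| Depends on baseline QoL, same in both arms | 7.00 (96.1%) | 5.59 (88.5%) | 7.00 (90.3%) | 6.99 (94.3%) |
| Depends on the 6-month score, control arm only | 3.52 (59.8%) | 4.15 (65.1%) | 4.37 (62.0%) | 4.37 (71.5%) |

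In the first row the regression method reports a mean SE of 1.68 against an actual 2.04. Its interval is then 2.01 × 1.68 = 3.4 points either side, where 2.01 × 2.04 = 4.1 is needed. The observed-data SE is 2.05, also 4.1 either side. On the graph, regression imputation would therefore look more precise than the observed data.

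Multiple imputation is close to nominal. Its mean SE of 1.94 against 2.04 is slightly low; the simulated imputation model had no breast-unit term, which is a likely reason.

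In the last row the four results lie within 0.9 points of each other (3.5 to 4.4), yet all are far from 7. That is the agreement a reader could mistake for robustness.

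**The case against.** The strongest reply is that a sound method is already planned. Multiple imputation stands in the same sentence as the other two, and it performed well whenever missingness was random or depended on baseline. An observed-data primary analysis with multiple imputation as a check is a common and defensible choice. This reply stands, and it limits the point to the two weak methods and to what the set as a whole can show.

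Several stronger readings are tempting but are not supported:

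- *The missing-data plan cannot test robustness at all.* The observed-data analysis, LOCF and multiple imputation rest on different assumptions, and comparing them is a limited check of missing-completely-at-random against missing-at-random. What is absent is a controlled departure from missing-at-random.
- *The trial's type I error is 9-11%.* That rate belongs to one sensitivity interval, and only if the imputation is deterministic, which the article does not state. The planned estimate is the GEE coefficient with its own interval, and no decision is tied to the sensitivity display.
- *The observed-data GEE is valid only if dropout is unrelated to QoL.* The arm difference was unbiased in the simulation when dropout depended on baseline QoL equally in both arms. Bias appeared when dropout depended on the outcome in one arm only, and nothing in the article shows that this will happen.
- *Women who died would be given a QoL score.* The article does not say how deaths are treated.

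A statistical analysis plan may specify the imputation model, its predictors, the handling of deaths and an analysis under missing-not-at-random. Their absence from an article is no finding in itself. But such detail would not repair the naming of LOCF and regression as equals of multiple imputation.

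**Conclusion.** The concern holds for the sensitivity set, not for the primary analysis. Followed as written, the plan would display one estimate that is generally biased and, if regression imputation is deterministic, one interval that is too narrow, both unranked beside a valid method.

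- **LOCF:** a 7-point difference becomes about 5.6 if baseline is carried, at 20% equal loss. The shrinkage is smaller, and may vanish, if the 6-week score already carries the effect. In these scenarios the bias is towards no difference, so LOCF would not create false significance.
- **Regression imputation:** SE about 13-18% too small and coverage about 89-91%, for an assumed correlation of 0.6 to 0.3. The clustered simulation gave 88-90%.
- **Whole set:** under outcome-dependent missingness in one arm, all results fell together at 3.5 to 4.4 against a true 7. This is an illustration of what agreement cannot show, not a forecast for this trial.

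The consequence is a misleading robustness display on the primary endpoint. It is a modest point, worth correcting because the remedy is cheap.

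**What to change.** Amend *Missing primary outcome data* as follows, and carry the wording into the analysis plan:

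1. Remove LOCF and single regression imputation from the sensitivity set.
2. Keep multiple imputation and name it as the main missing-data check. The imputation model should respect breast unit and include baseline and 6-week global QoL.
3. Add a delta-adjusted version of that multiple imputation, in which imputed scores are shifted by a stated range, separately by arm, to test robustness to missing-not-at-random. A range such as 0 to −10 points would span the 7-point target difference.
4. Plot these results beside the observed-data estimate, each labelled with its assumption.

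The observed-data GEE can remain the primary analysis; making multiple imputation or a mixed model primary is a trade-off for the trial team, not a correction. The cost is a few sentences and modest programming. All the scores needed are already scheduled for collection, and the sample size does not change.

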### Process evaluation

Running alongside the main study, a detailed mixed methods process evaluation is being undertaken at 16 sites to assess the implementation of the DESIs (fidelity to the trial protocol) to consider the DESIs’ usefulness and acceptability and examine the facilitators and barriers to embedding them into everyday clinical practice. A random selection of breast units was made stratified by trial arm and recruitment rate to the cohort study (high/low PET/surgery/chemo rates).

In summary, the Age Gap study^21^ aims at improving outcomes of older women diagnosed with breast cancer by providing high-quality evidence to support treatment decision making in this age group. The two evidence-based DESIs each include a clinical management algorithm and two PtDAs in the form of a booklet and a (brief) option grid for the clinical decision in question. These online algorithms will allow patient age, comorbidities, frailty and cancer characteristics to be considered by a clinician in predicting survival and cancer outcomes and to help inform breast cancer management decisions for older women.
